### Enrollment

Screening and enrollment visits will occur sequentially or on the same day. Study staff will collect baseline information on participants (e.g., demographics, medical history, obstetric history, history of respiratory illnesses) (Tables 1 and 2). Pregnant individuals who meet all eligibility criteria will be enrolled. Infants born to pregnant individuals will become study participants upon delivery and maternal consent. Postpartum individuals who meet all eligibility criteria will be enrolled along with their infants. Once enrolled, each individual will be registered in a study database. Enrollment will continue until number of participants is reached for a particular vaccine type/study group. If new vaccines receive EUA or licensure, vaccine types will be added.

### Follow-up

For women enrolled during pregnancy, a pre- and post-vaccination serology will be obtained if the subject had not received a vaccine prior to screening/enrollment, and post-vaccination serology will be obtained at any time after receipt of vaccine at the time of screening/enrollment if the subject had previously completed their full vaccination series. Routine follow-up visits for the women and infants include hospital delivery date, 2 weeks, 2, 6, and 12 months postpartum. Routine visits for postpartum women and their infants include visits at 2 weeks postpartum (or earliest enrolled date), 28 days (+/− 14) after last vaccination/ ≤3 months postpartum, 6 and 12 months postpartum. All routine visits will consist of obtaining updated clinical data, concomitant medications, collection of venous blood for antibody assays, obtaining date(s)/type of COVID-19 vaccine, date and severity of confirmed COVID-19 illness, and optional collection of breast milk samples (Tables 1 and 2). Unscheduled visits may be needed to complete study procedures that could not be conducted at the routine visits.

### Study outcomes

Outcomes of pregnancy, both maternal and fetal/infant, will be collected. Since this is an observational protocol, no serious adverse events (SAEs) or adverse events of special interest (AESIs) will be collected during this study. Potential non-serious adverse events that could occur in association with study procedures such as blood sample collection will be reported to the IRB. Maternal outcomes that will be recorded include death of mother or fetus, maternal hospitalization or prolonging of existing hospitalization, or important medical events reported after vaccination requiring treatment. Infant outcomes that will be recorded include neonatal or infant death through 12 months post-delivery, infant hospitalization, a congenital defect or genetic anomaly, preterm delivery/prematurity (defined as live birth prior to 37 weeks gestation). The assessment of these maternal and infant events will be harmonized by using existing Brighton Collaboration case definitions [15].

Pregnancy outcome data include the type of delivery (e.g., vaginal vs. Cesarean section), and any complications during labor and delivery for both the mother as well as the neonate. Neonatal assessments include but are not limited to gestational age, birth weight, Apgar scores, congenital and genetic abnormalities, infection, hematological and metabolic complications, admission to nursery or NICU and the need for respiratory support or other life sustaining interventions.

All information on COVID-19 cases during the study will be collected via medical records including polymerase chain reaction (PCR) or antigen testing results and severity of illness.

### Laboratory assays

#### Serum

Primary and secondary endpoint assays to determine serum levels of total and SARS-CoV-2 antigen-specific immunoglobulin G (IgG) [16] and live [17] and pseudovirus [ 18] neutralizing antibodies will be performed at central IDCRC laboratories utilizing qualified assays (Table 4). Reagents will include vaccine-matched and emerging variants to evaluate the ability of variants to escape antibody generated by vaccine in this cohort. Additional exploratory endpoint analyses may include Ig subclass, and SARS-CoV-2 IgG Fc glycosylation (Table 4) [20].

**Table 4 Tab4:** Assays

Study Endpoint	Specimen	Assay	Readout
Primary	Venous and Cord Blood Serum	MSD**®** V-Plex SARS-CoV-2 Panel 2 [16]	Spike, RBD and N IgG binding Ab
		FRNT-mNG [17]	Ab neutralizing SARS-CoV-2
		Pseudoneutralization [18]	Ab neutralizing SARS-CoV-2
Secondary	Breast Milk	MSD**®** V-Plex SARS-CoV-2 Panel 2 [16]	Spike, RBD and N IgG and IgA binding Ab
		FRNT-mNG [17]	Ab neutralizing SARS-CoV-2
		Pseudoneutralization [18]	Ab neutralizing SARS-CoV-2
Exploratory	Venous and Cord Blood Serum; Breast Milk	MSD**®** V-Plex SARS-CoV-2 Panel 2 [16] – emerging variant reagents	Vaccine-induced Ab binding to emerging variants
		FRNT-mNG [17] - emerging variant reagents	Vaccine-induced Ab neutralizing emerging variants
		Pseudoneutralization [18] - emerging variant reagents	Vaccine-induced Ab neutralizing emerging variants
		Luminex [19] or MSD**®**	Antigen-specific Ab isotype and subclass profiles
		IgG glycan analysis [20]	IgG Fc glycosylation
Ancillary^a^	Whole Blood	RNAseq, single-cell RNAseq [21]	Gene signatures to identify vaccine biomarkers
	PBMC	ELISpot/flow cytometry [22–24]	T and B memory cells, plasmablasts
		ICS/flow cytometry [25]	CD4/CD8 T cells
		Tetramer-staining	SARS-CoV-2 specific T cells
		MSD**®** cytokine panel	Th1/Th2 cytokines

*Abbreviations*: *MSD* Meso Scale Discovery®, *RBD* receptor binding domain, *FRNT-mNG* Focus Reduction Neutralization Test mNeonGreen, *Ab* antibody, *ICS* intracellular cytokine staining

^a^Collection of whole blood and PBMC under consideration in a subset of participants and/or at a subset of sites

#### Breast milk

Measurement of total and SARS-CoV-2 antigen-specific immunoglobulin IgA (IgA) and IgG and live and pseudovirus neutralizing antibodies will be performed at the same central laboratories as with serum (see above and Table 4). These assays are being qualified using breast milk samples from vaccinated and/or COVID-19 infected women.

#### Other samples

The collection of whole blood and its processing for peripheral blood mononuclear cells (PBMC) in a subset of participants and/or subset of clinical sites are under discussion in order to conduct additional ancillary studies (Table 4).

### Data collection, quality and management

Data collection is the responsibility of the study personnel at the participating clinical study site under the supervision of the site PI. During the study, the site PI must maintain complete and accurate documentation for the study.

The site PI is responsible to ensure the accuracy, completeness, legibility, and timeliness of the data reported. All source documents should be completed in a neat, legible manner to ensure accurate interpretation of data.

Copies of the electronic Case Report Form (eCRF) will be provided for use as source CRFs, as needed, and maintained for recording data for each subject enrolled in the study. Data reported in the eCRF derived from source CRFs should be consistent or the discrepancies should be explained.

The data coordinating center for this study will be responsible for data management, quality review, analysis, and reporting of the study data.

Clinical (including, but not limited to, AEs, concomitant medications, medical history, physical assessments) and immunogenicity data will be entered into a 21 CFR 11-compliant Clinical Data Management System provided by the data coordinating center. The data system includes password protection and internal quality checks, such as automatic range checks, to identify data that appear inconsistent, incomplete, or inaccurate. Clinical data will be entered directly from the CRFs completed by the study personnel.

### Statistics

This study will generate descriptive data that is supportive of the hypothesis that COVID-19 vaccines elicit adequate immune responses among pregnant and postpartum individuals and will describe the transplacental antibody transfer for SARS-CoV-2 and serum SARS-CoV-2 antibodies in mother and infants of vaccinated mothers.

Approximately 200 pregnant individuals and their infants and up to 65 postpartum individuals and their infants per SARS-CoV-2 vaccine type (Groups 1–4) will be enrolled in this protocol. Two additional groups (Groups 5 and 6) have been added since beginning enrollment following approval of administration of a booster dose in late 2021. It is important to generate data on kinetics and durability of maternal and infant antibodies for all vaccine regimens, including those with additional doses beyond the primary series administered during pregnancy. Figure 1 illustrates the study precision of estimation of GMT of Neut antibodies the study with various sample sizes using Phase 1 data from the Pfizer, Moderna, and Janssen COVID-19 vaccines [26–28]. In addition, there will be good precision for estimation of transplacental transfer ratios.

**Fig. 1 Fig1:**
[figure not shown]
Sample Size Calculation based on Width of 95% Confidence Intervals for Neutralizing Antibodies for COVID-19 Vaccines included in MOMI-Vax. Legend: The curve shows neutralizing antibody from Phase 1 studies and demonstrates the inflection point for sample size at approximately 150 individuals per group, with little gain in precision with higher samples sizes. Results similar using binding antibody data (results not shown)

The analysis groups are:Group 1: Individuals who receive a COVID-19 vaccine during pregnancy (up to 200 individuals per vaccine type).Group 2: Individuals who receive a COVID-19 vaccine postpartum (up to 65 individuals per vaccine type).Group 3: Infants of individuals who receive COVID-19 vaccine during pregnancy (approximately 200 infants per vaccine type).Group 4: Infants of individuals who receive COVID-19 vaccine postpartum (approximately 65 infants per vaccine type).Group 5: Individuals who receive additional COVID-19 vaccine(s) (booster) during pregnancy (up to 200 individuals).Group 6: Infants of individuals who received additional COVID-19 vaccine(s) (booster) during pregnancy (approximately 200 infants).

The study will not randomize participants between vaccines, and statistical analyses will seek to adjust for covariates when deemed appropriate to account for potential confounders. All analyses will be done by vaccine type and/or platform or vaccination regimen on all available data, and analyses for each endpoint are outlined in Table 5. Multiple imputation may be used if there is substantial missingness. Additional analysis details will be included in a statistical analysis plan.

**Table 5 Tab5:** Primary, Secondary and Exploratory Objectives, Endpoints and Analyses

	Objectives	Endpoints	Analyses
**Primary**	1. Immunogenicity: To describe kinetics and durability of maternal serum antibodies following receipt of COVID-19 vaccine in individuals vaccinated during pregnancy, by vaccine type and platform.	• Geometric Mean Titer (GMT) of serum immunoglobulin G (IgG) enzyme-linked immunosorbent assay (ELISA) and neutralizing (Neut) antibodies after vaccination and up to 12 months after delivery, by vaccine type and platform^a^	• Geometric Mean Titers (GMTs) and 95% Confidence Intervals (CIs) will be calculated in Group 1. Plots such as reverse cumulative distributions or longitudinal presentations of GMTs will be presented.
	2. Immunogenicity: To describe the transplacental antibody transfer of SARS-CoV-2 antibodies among individuals vaccinated during pregnancy, overall and by vaccine type and platform.	• GMT and ratio of cord blood to maternal serum IgG ELISA and Neut antibodies overall and by vaccine type and platform.	• GMTs and ratio of cord blood to maternal serum and 95% CIs will be calculated in Group 1.
	3. Immunogenicity: To describe kinetics and durability of serum SARS-CoV-2 antibodies in infants of mothers vaccinated during pregnancy, by vaccine type and platform.	• GMT of serum IgG ELISA and Neut antibodies at birth (cord blood) and at approximately 2 and 6 months of age in all infants, by vaccine type and platform.	• GMTs and 95% CIs will be calculated in Group 3. Plots such as reverse cumulative distributions or longitudinal presentations of GMTs will be presented.
**Secondary**	1. Safety: To describe pregnancy outcomes in individuals who receive COVID-19 vaccine during pregnancy or postpartum, and their infants, by vaccine type and platform.	• Frequency of maternal and infant outcomes vs. background rates in the US, overall and by vaccine type and platform.	• A comparison of frequencies to background rates will be reported in Groups 1–4 (no formal statistical testing).
	2. Immunogenicity: To evaluate immune responses and durability of antibodies in individuals who received different COVID-19 vaccines during pregnancy or postpartum compared to non-pregnant populations of women of childbearing age and to a correlate of protection (if available), by vaccine type and platform.	• GMT of serum IgG ELISA and Neut antibodies after vaccination in pregnancy or postpartum vs. mean titers achieved by non-pregnant participants in clinical trials and to a correlate of protection if available, by vaccine type and platform.	• One sample t-tests will be done in Group 1.
	3. Immunogenicity: To assess the effect of gestational age at vaccination (trimester of gestation), maternal age, health and risk status, on immune responses and durability of antibodies in individuals who receive different COVID-19 vaccines during pregnancy or post-partum, by vaccine type and platform.	• GMT of serum IgG ELISA and Neut antibodies after vaccination in pregnancy by gestational age at vaccination (trimester of gestation) and interval between vaccination and delivery, by vaccine type and platform. GMT of serum IgG ELISA and Neut antibodies after vaccination in pregnancy or postpartum by maternal age, health status, and risk status (e.g., occupation, priority vaccination group) overall and by vaccine type and platform.	• GMTs and 95% CIs will be calculated for Group 1 by strata. Student’s t-tests and linear regression (controlling for potential confounders) will be used to compare strata.
	4. Immunogenicity: To describe the transplacental antibody transfer of SARS-CoV-2 antibodies among individuals vaccinated during pregnancy, by gestational age at vaccination, by interval from vaccination to delivery and maternal age, health and risk status, overall and by vaccine type and platform.	• GMT and ratio of cord blood to maternal serum IgG ELISA and Neut antibodies at delivery by gestational age at vaccination (trimester of gestation) and interval between vaccination and delivery, overall and by vaccine type and platform. • GMT and ratio of cord blood to maternal serum IgG ELISA and Neut antibodies at delivery by maternal age, health status, and risk status, overall and by vaccine type and platform.	• GMTs and ratios of cord blood to maternal serum and 95% CIs will be presented for Group 1 by strata. Student’s t-tests and linear regression (controlling for potential confounders) will be used to compare strata.
	5. Immunogenicity: To describe the kinetics of SARS-CoV-2 antibodies in breast milk of mothers who received vaccine during pregnancy or postpartum, overall and by vaccine type and platform.	• GMT of IgG and immunoglobulin A (IgA) ELISA and Neut antibodies in breast milk at approximately 2 weeks, and 2, 6, and 12 months postpartum, in individuals vaccinated during pregnancy or postpartum, overall and by vaccine type and platform.	• GMTs and 95% CIs will be calculated in Group 1. Plots such as reverse cumulative distributions or longitudinal presentations of GMTs will be presented.
	6. Immunogenicity: To describe the kinetics and durability of maternal serum antibodies following receipt of COVID-19 vaccine in individuals vaccinated postpartum, by vaccine type and platform.	• Postpartum individuals: GMT of serum IgG ELISA and Neut SARS-CoV-2 antibodies pre- and/or post-vaccination, and at approximately 2, 6, and 12 months after delivery, overall, and by vaccine type and platform.	• GMTs and 95% CIs will be calculated in Group 3. Plots such as reverse cumulative distributions or longitudinal presentations of GMTs will be presented.
	7. Immunogenicity: To describe the kinetics and durability of serum SARS-CoV-2 antibodies in infants of individuals vaccinated postpartum, by vaccine type and platform.	• GMT of serum IgG ELISA and Neut antibodies at approximately 2 and 6 months of age in infants of postpartum individuals, overall and by vaccine type and platform.	• GMTs and 95% CIs will be calculated in Group 4. Plots such as reverse cumulative distributions or longitudinal presentations of GMTs will be presented.
**Exploratory**	1. To describe the effectiveness of COVID-19 vaccines against maternal COVID-19 infection during pregnancy and postpartum.	• Incidence of laboratory confirmed COVID-19 and severity of disease during study participation assessed through passive surveillance in individuals vaccinated during pregnancy or postpartum vs. rates in unvaccinated population of women of childbearing age, overall and by vaccine type and platform.	• Incidence rates and 95% CIs will be calculated in Groups 1 and 3.
	2. To describe the effectiveness of maternal antibodies to provide protection against SARS-CoV-2 infection/symptomatic disease/severity in infants in the first 12 months of life.	• Incidence of laboratory confirmed COVID-19 and severity of disease during study participation assessed through passive surveillance in infants of individuals vaccinated in pregnancy or postpartum vs. background rates in infants of unvaccinated population, overall and by vaccine type and platform.	• Incidence rates and 95% CIs will be calculated in Groups 2 and 4.
	3. To describe the effectiveness of breast milk antibodies to provide protection against SARS-CoV-2 infection/symptomatic disease/severity in infants in the first 12 months of life.	• Incidence of laboratory confirmed COVID-19 and severity of disease during study participation through passive surveillance in breastfed infants vs. not breastfed infants, by vaccine type and platform. • Incidence of laboratory confirmed COVID-19 and severity of disease during study participation through passive surveillance in breastfed infants of individuals vaccinated during pregnancy vs. postpartum, overall and by vaccine type and platform.	• Incidence rates and 95% CIs will be calculated in Groups 2 and 4.

*Abbreviations*: *GMT* Geometric Mean Titer, *IgG* immunoglobulin G, *ELISA* enzyme-linked immunosorbent assay, *Neut* neutralizing, *IgA* immunoglobulin A

^a^Pregnant individuals: pre- and/or post-vaccination, at delivery, and at approximately 2, 6, and 12 months postpartum

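### Secondary 2 tests Group 1 titers against outside-trial means that are tied neither to the objective's population nor to the cohort's assays, so an assay or population difference could be reported as an effect of pregnancy

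*Protocol article*

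**What the plan says.** All three cells of the Secondary 2 row in Table 5 (Statistics section) matter here.

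- **Objective:** immune responses and durability are to be "compared to non-pregnant populations of women of childbearing age", and to a correlate of protection if one exists.
- **Endpoint:** the reference is "mean titers achieved by non-pregnant participants in clinical trials". No sex or age limit is given.
- **Analysis:** "One sample t-tests will be done in Group 1". Group 1 is the women vaccinated in pregnancy, up to 200 per vaccine type.

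Under Laboratory assays, Serum, the primary and secondary endpoint assays "will be performed at central IDCRC laboratories utilizing qualified assays". Table 4 lists the MSD V-Plex panel for binding antibody, FRNT-mNG for live-virus neutralization and a pseudovirus neutralization assay.

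The article does not say which trials supply the reference, on which assay or in which unit. Secondary 1, one row above, also sets cohort results against outside figures, but states that these will not be formally tested.

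**The concern.** A one-sample test treats the reference as a known constant on the same scale and for the population of interest. The row as written secures neither condition. The endpoint's comparator is wider than the objective's and could take in men and women past childbearing age. The cohort's titers come from the study's own central laboratories, while the reference may come from another assay or laboratory.

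Secondary 2 is the row that sets the response in pregnancy against the response outside it, and the Background section expects the results to inform policy and personal decisions. A false finding of lower or higher titers in pregnancy would therefore matter. A mismatch could equally hide a true difference. Enrolling more women does not shrink such a bias. It only narrows the interval around the wrong value.

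**Working it through.** **No figure to reproduce.** The article states no power, SD, reference titer or detectable difference for Secondary 2. Fig. 1 is not visible, and no SD is given in the text.

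**What the test estimates.** On the log10 scale, the expected difference between the Group 1 mean and the outside reference is

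D = δ + α + π

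where δ is the pregnancy effect, α the assay or laboratory scale difference and π the population difference (sex and age mix). Group 1 data and one external constant identify only the sum D. If δ = 0, the test still rejects whenever α + π is large enough. If δ = −log10(1.2) and α + π = +log10(1.2), then D = 0 and a real reduction is hidden.

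**Whether covariates help.** The Statistics section says that analyses will adjust for covariates when appropriate, in a sentence about the lack of randomization between vaccines. A one-sample t-test against a constant has no covariates. A model fitted within the cohort cannot estimate α either, because every cohort serum is on the cohort's own scale.

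**Illustration of size.** Inputs:

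- n = 200: the stated upper limit for Group 1 per vaccine type.
- Level: two-sided 5%, assumed, because the article gives none for this test.
- log10 SD: 0.3, 0.4 and 0.5, assumed.
- Shift r = 10^(α+π): 1.2-fold and 1.5-fold, assumed.
- δ = 0.

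The rejection probability comes from the non-central t distribution with n − 1 = 199 degrees of freedom and non-centrality

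λ = log10(r) / SD × √n

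Here log10(1.2) = 0.0792, log10(1.5) = 0.1761 and √200 = 14.14.

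| SD | λ at 1.2-fold | Declared significant | λ at 1.5-fold | Declared significant |
|---|---|---|---|---|
| 0.3 | 3.73 | 96.0% | 8.30 | about 100% |
| 0.4 | 2.80 | 79.6% | 6.23 | about 100% |
| 0.5 | 2.24 | 60.6% | 4.98 | 99.9% |

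With no shift the rate is 5%, as it should be.

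**Effect of enrolment.** With SD 0.4 and a 1.2-fold shift, the rate is 50.0% at n = 100, 67.3% at n = 150 and 79.6% at n = 200. The artefact becomes more certain as the group fills.

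**The case against.** The strongest reply is that the article condenses a fuller protocol and defers details to a statistical analysis plan. That plan may name a reference trial that used a matching assay, or convert units. This is fair, and it defeats the stronger reading that a mismatch will occur or that the test will mainly detect assay scale. The documents show neither. They show only that the row, run as written, offers no protection. The external comparator, its wide population and the formal test are all fixed in the article.

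The endpoint's wording may also merely name a data source, with the objective setting the population. That reading is possible, and nothing says that men or older adults will be included. Even so, two cells of one row differ, and an analyst could follow either.

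The illustration shows what any test does when the means differ. That is true, and it is not evidence that a shift exists or how large it is.

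The analysis is secondary, the primary analyses are descriptive and no decision rule hangs on this p-value. That limits the importance of the point but leaves the defect in place.

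Two further inferences should be resisted:

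- A reader might take the ELISA label on the binding endpoint, set against MSD in Table 4, as proof of an assay mismatch. The label runs through Table 5, primary endpoints included, and says nothing about the comparator's assay.
- A reader might extend the error rates to the postpartum women, who appear in the objective. The stated test covers Group 1 only, so no rate is given for the postpartum group.

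**Conclusion.** The concern holds as a possibility that the plan leaves open. The comparator in the endpoint is broader than the one in the objective, nothing links the reference titer to the cohort's assays, and the planned test cannot separate a pregnancy effect from an assay or population difference. Such a difference could be reported as an effect of pregnancy. Whether it would be depends on a choice of reference that the article does not show.

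The rates of 96% to 61% for a 1.2-fold shift, and almost 100% for 1.5-fold, rest on assumed SDs, assumed shifts, full enrolment of 200 and a two-sided 5% level. They show how little mismatch would be enough, and are not predictions for this study. The change is worth making before analysis, because it is cheap and this row carries the comparison between pregnant and non-pregnant women.

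**What to change.** Amend the Secondary 2 row of Table 5, and carry the change into the statistical analysis plan:

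1. Restrict the endpoint's comparator to non-pregnant women of childbearing age, so that it matches the objective.
2. Run the test only where the reference titer comes from the same assay as the cohort's, or where both sides can be expressed in the same reference units.
3. Where either condition fails for a vaccine or assay, show the outside value for context with no formal test and no statement about pregnancy, as Secondary 1 does with background rates.

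The cost is wording, unit conversion where possible and a request to the reference trials for subgroup summaries, which may not always be available. No new participants or samples are needed, and comparator sera need not be retested, because rule 3 covers the cases that cannot be matched. The downside is that some vaccine-by-assay comparisons will lose their p-value.

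### Secondary objective 2 tests Group 1 against an external trial mean with a one-sample t-test, which omits that mean's own sampling error and inflates the type I error

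*Protocol article*

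**What the plan says.** The row for Secondary objective 2 in Table 5 (Statistics section) has three relevant parts.

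- The objective is to evaluate responses "compared to non-pregnant populations of women of childbearing age and to a correlate of protection (if available), by vaccine type and platform".
- The endpoint sets Group 1 titers against "mean titers achieved by non-pregnant participants in clinical trials and to a correlate of protection if available".
- The analysis cell reads, in full: "One sample t-tests will be done in Group 1".

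The row therefore has two comparators, an external mean and a threshold, and one test for both. It does not name the reference trial, its size or its SD, and it specifies no confidence interval for this comparison.

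Group 1 is capped at 200 women per vaccine type. The Statistics section says that Table 5 outlines the analysis for each endpoint and leaves further detail to a statistical analysis plan.

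On timing, the Follow-up section says that for women who had already completed their series at enrollment "post-vaccination serology will be obtained at any time after receipt of vaccine at the time of screening/enrollment". Women not yet vaccinated at enrollment give pre- and post-vaccination samples.

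**The concern.** A one-sample t-test divides the observed difference by the standard error of the Group 1 mean alone. That is right when the reference is a fixed number. The mean titer of non-pregnant trial participants is an estimate from a finite sample, so the true standard error of the difference is larger than the one the test uses. The test is then anti-conservative for every finite reference size.

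This is the row that asks whether women vaccinated in pregnancy respond as non-pregnant women do, and the Background expects the results to inform policy and personal decisions. If the true responses were equal, the named test would declare a difference, in either direction, more often than its nominal level suggests.

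The row above it in Table 5 makes a useful contrast. Secondary objective 1 also sets study data against external figures, but it rules out formal testing. Secondary objective 2 tests formally against an external figure without allowing for that figure's error.

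**Working it through.** The article gives no alpha, power, SD, reference size or error rate for this test, so there is no stated figure to reproduce. The check below measures how large the omission could be.

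**Inputs**
- n = 200: the Group 1 ceiling per vaccine type (analysis groups, Statistics section).
- Nominal two-sided level 5%: assumed.
- m, the number of reference participants: assumed, varied from 15 to 5000.
- Equal log-titer SD, s, in both populations: assumed, then relaxed.

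**Formula**
- Variance the test uses: s²/n.
- True variance of the difference: s²/n + s²/m = (s²/n)(1 + n/m).
- The true standard error is therefore f = √(1 + n/m) times the one used.
- Actual type I error = 2 × [1 − Φ(1.96/f)].

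Example at m = 200: f = √2 = 1.41, 1.96/1.41 = 1.39, and the two-sided error is 0.166.

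**Results, n = 200**

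| m (assumed) | f | Actual type I error |
|---|---|---|
| 15 | 3.79 | 0.605 |
| 50 | 2.24 | 0.381 |
| 100 | 1.73 | 0.258 |
| 200 | 1.41 | 0.166 |
| 500 | 1.18 | 0.098 |
| 1000 | 1.10 | 0.074 |
| 2000 | 1.05 | 0.062 |
| 5000 | 1.02 | 0.055 |

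A simulation of the one-sample test (20,000 runs each) agrees: 0.607 at m = 15, 0.378 at m = 50, 0.163 at m = 200 and 0.073 at m = 1000.

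**How large must the reference be?** Setting the error to a target a gives f = 1.96/z, with z the 1 − a/2 normal quantile, and m = n/(f² − 1). With n = 200, the error falls to 10% only at m of about 476, and to 6% only at about 2327.

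**Sensitivity**
- If the reference SD is r times the Group 1 SD, f = √(1 + r²n/m). At m = 200 the error is 0.108 for r = 0.7 and 0.277 for r = 1.5.
- A smaller Group 1 reduces the inflation. With n = 100 and m = 200, f = √1.5 = 1.22, 1.96/1.22 is about 1.60, and the error is about 11%.

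**Does a two-sample comparison repair it?** A Welch test at n = 200 (5,000 simulated runs each) gave 0.055 at m = 15, 0.051 at m = 50 and 0.048 at m = 200.

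The price is sensitivity. The difference detectable with 80% power is 2.80 × √(1/n + 1/m) in SD units. It rises from 0.198 under the one-sample formula to 0.750 at m = 15, 0.443 at m = 50, 0.280 at m = 200 and 0.217 at m = 1000.

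**The case against.** The best defence is that the study is mainly descriptive, that no alpha or decision rule attaches to this test, that no primary endpoint or sample size depends on it, and that a statistical analysis plan is promised. This stands as an argument about severity. It does not rescue the method: the article names a test, and an analysis plan that carried the reference's error would have to replace that test rather than add detail to it.

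A second defence is that the row also covers a correlate of protection. That stands too. Against a fixed threshold the one-sample test is the usual choice.

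Some stronger readings are tempting but are not supported.

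- A reader might infer that the p-values are far too optimistic because the reference must be a small early-phase cohort. The Statistics section does plan precision "using Phase 1 data from the Pfizer, Moderna, and Janssen COVID-19 vaccines", but only for that purpose. Table 5 says only that the reference comes from clinical trials. With a reference of 2000 or more the inflation is slight.
- A reader might extend the criticism to the plan's confidence intervals. This row specifies none.
- A reader might take the titers in the endpoint to be arithmetic means, or make something of the label ELISA in Table 5 against the MSD panel in Table 4. The first is a guess about a condensed table cell. The second is a matter of labelling that recurs through Table 5. Neither bears on the test.
- A reader might assume that the 28 ± 14 day window in the Follow-up section fixes the timing of the Group 1 samples. It is stated there for postpartum women. The readable text gives no such window for Group 1, and the Table 1 schedule is not shown.

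**Conclusion.** Wrong as written, and should be fixed. For the comparison with non-pregnant trial participants, the named test treats an estimated mean as known, and its type I error exceeds nominal for any finite reference.

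The direction of the error is certain and its size is not. It is severe if the reference has tens of participants, clear at a couple of hundred, and small in the thousands. The figures assume a nominal two-sided 5% level, a full Group 1 of 200 and equal SDs. The reference size is an assumption throughout.

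The finding does not extend to a test against a fixed correlate of protection, and it touches no primary analysis.

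**What to change.** In Table 5, Secondary objective 2, and in the analysis plan, separate the two comparators.

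1. **Non-pregnant reference.** Replace the one-sample t-test with a geometric mean ratio and 95% CI from a two-sample Welch comparison on the log scale. Use the reference cohort's own n and log SD, or recover its standard error from the published CI. Name the reference trial for each vaccine type. Use Group 1 samples taken at a time since last dose comparable with the reference trial's visit.
2. **Correlate of protection.** Keep the one-sample test only where the correlate is a fixed threshold.

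The cost is a change of wording, with no new data collection: published summary data from the reference trial are enough. The intervals will be wider, and fewer Group 1 samples will qualify once timing is matched. The change corrects the variance only. Differences in assay or population between this cohort and the external trials remain, and the report should say so.
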